## Abstract

**Background:**

Osteoarthritis (OA) is a leading cause of disability in developed nations. Total knee arthroplasty (TKA) is a clinically effective treatment for people with end-stage knee OA, and represents one of the highest volume medical interventions globally. However, up to one in three patients remain dissatisfied following TKA. Research indicates that the strongest predictor of patient dissatisfaction following TKA is unmet expectations. This study will use a discrete choice experiment (DCE) provided to patients to improve knowledge of the expected outcomes of TKA. This increased knowledge is based on actual outcome data and is hypothesised to optimise patient expectations of TKA outcomes, thereby increasing their satisfaction and self-reported health outcomes.

**Methods/design:**

One hundred and thirty-two people with end-stage OA on the waiting list for TKA will be recruited and randomly allocated to one of two groups using computer-generated block randomisation. A randomised controlled trial (RCT) adhering to SPIRIT and CONSORT guidelines will evaluate the effect of administering a DCE prior to surgery on patient-reported pain and function and satisfaction following TKA. Patients in the intervention arm will complete a survey containing the DCE, compared to the control group who will complete a modified survey that does not contain the DCE activity. The DCE contains information on actual risks of postoperative complications, as well as health status after TKA. The DCE encourages patients to actively make trade-offs between risks and health outcomes to elicit their preferences. Participants in both groups will be required to complete the survey after consenting to have the procedure, but prior to surgery during their routine preadmission appointment at St. Vincent’s Hospital, Melbourne, Australia (SVHM). Patients in both the intervention and control groups will also be required to complete a brief patient expectation survey 1 week prior to scheduled TKA. In addition, orthopaedic surgeons will complete a brief expectations survey for each patient consented for TKA to compare matched surgeon and patient expectations for recovery following TKA. Primary outcomes will be evaluated by a blinded examiner at 12 months post surgery using a validated self-reported pain and physical function scale, and a validated patient satisfaction scale. Secondary outcomes will include a range of validated measures of health and psychological wellbeing. All analyses will be conducted on an intention-to-treat basis using linear regression models.

**Discussion:**

This study is the first of its kind to use a DCE to provide information to patients to optimise their expectations of the outcomes of surgery. Reducing the rate of patient dissatisfaction commonly seen in patients following TKA will help to reduce the burden associated with poor outcomes on the health system.

**Trial registration:**

Australian New Zealand Clinical Trials Registry (ACTRN12615001226594p). Version 1; registered on 9 November 2015.

**Electronic supplementary material:**

The online version of this article (doi:10.1186/s13063-016-1536-5) contains supplementary material, which is available to authorized users.

## Background

Osteoarthritis (OA) is one of the most disabling diseases in developed countries and is responsible for significant functional limitation in over 43 million people worldwide, 27 million of whom are 60 years of age or older [1]. Age is the strongest predictor of the development and progression of OA, and as such the number of people suffering with OA is expected to increase over the coming years due to population ageing [2]. Total knee arthroplasty (TKA) is a cost-effective treatment for people with end-stage knee OA [3] that improves quality of life by reducing pain, joint deformity and loss of function. It is a high-cost [4, 5] and high-volume procedure [6], which dominates national surgical waiting lists. The number of TKAs being performed each year has risen markedly over the past decade and on average has doubled in most Organization for Economic Co-operation and Development (OECD) countries [2]. In Australia, nearly 50,000 people underwent TKA in 2014 at an estimated cost exceeding Australian $1 billion [5, 6].

Many studies have confirmed the beneficial impact of TKA on pain, disability and quality of life on average [7, 8]; however, surgery is not without risk, and not without heterogeneity in outcomes. In the short-term postoperative period, there is a small risk of severe complications [9–11] and in the longer term there is the risk of prosthesis failure, primarily through loosening, resulting in the need for complex revision surgery [6]. While survival analysis is crucial for understanding the failure rate of TKA, revision surgery alone as a sole index of failure has been called into question because of the potential for underestimating the problem [12]. In this regard patients with joint pain and dysfunction may endure years of dissatisfaction without undergoing revision surgery, with reports suggesting that 15–30 % of patients are dissatisfied despite the procedures being technically and radiologically satisfactory [13].

Not all patients undergoing TKA are at equal risk of complications. A number of patient factors can increase the risk of complications for individuals undergoing TKA, including: age and gender [14], body mass index [9, 10], ethnicity [15], psychological distress [16, 17], baseline pain and functional disability [14], comorbidity profile [9, 14] and radiographic OA severity [14]. For individuals considering TKA as a treatment option very little is known about patients’ perspectives on acceptable level of risk and how closely aligned or not this risk is with their treating clinicians’.

Although patients and clinicians share similar goals of maximising treatment benefits while minimising risk, they may have different perspectives on trade-offs among benefits and risks of treatment [18]. The acceptable level of risk tolerated by a patient depends not only on the benefits provided by the TKA (significant pain relief and improvement in joint function) but also on the seriousness and severity of the disease, the availability of other treatments and other factors such as risk of complication [19]. To date, patients’ assessments of risks and benefits of surgical interventions have not been subjected to rigourous evaluation. This is important because unrealistic patient expectations and uninformed perceptions of potential benefits, risks and limitations of surgery lead to dissatisfaction following TKA [20].

It has been shown that more than one half of patients undergoing TKA have expectations of surgery that exceed those of their surgeons; in contrast, only one quarter expect less than their surgeons [21]. Patients with higher levels of expectations than their surgeons anticipated greater improvements in activity levels and those with lower expectations anticipated a higher incidence of complications. It has also been reported that the rate of dissatisfaction amongst TKA recipients with unmet expectations is as high as 49 % compared to 6 % in those whose expectations have been met [13].

This study will use a discrete choice experiment (DCE) as an intervention to provide patients with more realistic expectations of the outcomes of TKA, specified in terms of operative and postoperative risks and improved function and quality of life. DCEs are choice models that describe, explain, and predict choices between two or more discrete alternatives, such as whether or not to undergo surgery. The DCE is administered as part of a survey, where patients are asked to compare a series of hypothetical (but realistic) scenarios that describe risks and outcomes of TKA, and asked to choose which they would prefer [22]. By asking individuals to choose between scenarios, the DCE elicits patients’ willingness to accept trade-offs between features of specific treatments with different characteristics, thereby revealing their preferences in terms of the relative importance of each characteristic of the treatment [23, 24]. The impact of administering a DCE prior to TKA on quality of life and satisfaction post surgery will be examined in a randomised controlled trial (RCT).

To date, patients’ assessments of risks and benefits of surgical interventions, and specifically TKA, have not been subjected to rigourous evaluation. The aim of this research is to use DCEs to (1) explore how patients with end-stage OA undergoing TKA balance risks and benefits, (2) evaluate the effect of information from the DCE on health outcomes and satisfaction following TKA, and (3) compare matched surgeon and patient expectations for recovery following TKA.

## Methods

### Experimental design

The design is a two-arm, blinded, randomised controlled clinical trial comparing satisfaction and health outcomes of TKA patients who are provided with a DCE prior to undergoing TKA, with that of a control group. Patients in the intervention arm will complete a survey containing the DCE. Patients in the control arm will complete a survey that does not contain the DCE activity. Patients will also complete a brief patient expectation survey 1 week prior to scheduled TKA. Outcomes will be compared at 12 months after TKA. In addition, orthopaedic surgeons will complete a brief expectations survey for each patient consented for TKA. This will allow for a matched surgeon/patient comparison of expectations for recovery following TKA. The study strategy is registered, constructed and presented according to the recommendations of the Standard Protocol Items: Recommendations for Interventional Trials (SPIRIT) [25] (see Additional file 1 SPIRIT checklist) and Consolidated Standards of Reporting Trials (CONSORT) guidelines [26].

### Participants

Patients will include those with end-stage OA who are on the waiting list at St. Vincent’s Hospital Melbourne, Australia (SVHM) and scheduled to undergo TKA. After patients have seen the orthopaedic surgeon and provided consent for TKA, they attend the orthopaedic preadmission clinic for medical optimisation prior to surgery. Potential patients will be identified and recruited for the study during their attendance at this clinic, where they undergo health assessment and education. The team comprises an orthopaedic surgeon, registrar medical officer and nursing and allied health staff. Eligible patients will include those who have had a previous TKA, in order to determine whether knowledge and experience gained through prior TKA will influence their response to the DCE activity. Orthopaedic surgeons and registrars will include those who perform TKAs at SVHM.

#### Inclusion criteria

These are (1) patients on the surgical waiting list for primary TKA for end-stage OA at SVHM, and (2) orthopaedic surgeons/registrars who consult at the orthopaedic clinics at SVHM.

#### Exclusion criteria

These are (1) patients undergoing revision surgery or surgery for neoplastic disease, and (2) inability to provide informed consent due to mental incompetence (e.g. intellectual disability, dementia).

### Intervention

Patients in the intervention arm will complete a survey containing the DCE. The DCE includes items about postoperative pain, stiffness, quality of life, complications and adverse events (health states) following knee replacement surgery. The remainder of the survey includes items about how much improvement in symptoms patients expect following knee surgery, the level of control, attitude towards taking risks, and the physical and emotional experiences associated with knee pain. Participants will be required to complete the survey prior to TKA during their routine preadmission appointment at SVHM. The survey will take approximately 30 min to complete. Patients will also be required to complete a brief patient expectation survey 1 week prior to scheduled TKA, which will take approximately 5 min to complete. Participants will complete the surveys electronically during their preadmission appointment. Surveys will be completed using a portable computer with administrative assistance provided from the study coordinator.

### Discrete choice experiment development

#### Attributes and levels

To determine attributes and their levels, we used (1) previous literature, (2) data from an existing consecutive cohort of patients who underwent primary elective TKA at SVHM between January 2006 and December 2012 (*N* = 2221, the St Vincent’s Melbourne Arthroplasty Outcomes (SMART) Registry), (3) 40 face-to-face patient interviews, and (4) feedback from experts in the field of orthopaedics and DCE development, including a professor of orthopaedics and Head of the Department of Surgery at SVMH; a professor of economics and Head of the Health Economics Research Programme at the University of Melbourne; the Head of Arthritis Research for the Department of Orthopaedics at SVHM; a rheumatologist at SVHM; and a general practitioner (GP). This resulted in six attributes, with three levels defined for each attribute (Table 1). Two attributes represented pain, two attributes represented physical function, and two attributes represented complications/risks associated with TKA.

**Table 1 Tab1:** Attributes and levels included in the discrete choice experiment

Attributes	Levels
Pain outcomes:	
1. Day-time pain 9–12 months after surgery	No day-time pain, moderate day-time pain, severe day-time pain
2. Night-time pain 9–12 months after surgery	No night-time pain, moderate night-time pain, severe night-time pain
Functional outcomes:	
3. Standing and walking on a flat surface 9–12 months after surgery	No difficulty standing and walking;
	Moderate difficulty standing and walking, severe difficulty standing and walking
4. Bending to floor, rising from sitting, going up and down stairs 9–12 months after surgery	No difficulty bending to floor, rising from sitting, going up and down stairs
	Moderate difficulty bending to floor, rising from sitting, going up and down stairs
	Severe difficulty bending to floor, rising from sitting, going up and down stairs
Risk of complications:	
5. Risk of having to go back into hospital and have a second operation on your knee	0 %, 7 %, 13 %
6. Risk of getting a complication that requires seeing GP or specialist for further treatment	0 %, 10 %, 21 %

For complication/risk attributes, data were derived from the SMART registry and used to identify the probabilities of the most frequent surgical risks and complications that occurred within 12 months of joint replacement surgery. Specifically, attributes for adverse events were subdivided into two categories: ‘Risk of having to go back into hospital and have a second operation on your knee’ and ‘Risk of getting a complication that requires seeing your GP or specialist for further treatment’. The levels for these absolute risk attributes were based on the minimum, median, and maximum rate of identified risks over the period of the SMART registry from 2006–2012.

For attributes related to measures of treatment efficacy in terms of pain and function following TKA, these were based on items derived from the Western Ontario and McMaster Universities (WOMAC) Osteoarthritis Index [27]. This is a widely used and validated questionnaire specifically designed to evaluate the response to knee OA treatment. Levels for these attributes were derived from existing data in the SMART registry of patient WOMAC scores at 12 months post surgery from all elective primary TKAs performed during 2012 at SVHM (*N* = 331).

#### DCE experimental design

The six attributes and corresponding levels described in Table 1 give rise to a possible combination of 729 (3^6^) treatment outcome scenarios. As this full factorial design of possible scenarios was not feasible to present to each patient, a sample was generated using a fractional factorial experimental design. An efficient design was generated using NGENE software, such that attributes were varied independently from one another across the scenarios and that standard errors were minimised. This model allows for multiple versions of the questionnaire, reducing the burden on patients and increasing the statistical efficiency of the study. Two versions of the DCE questionnaire were generated, each containing six different choice sets. Each DCE questionnaire had the same number of scenarios with the same attributes, but different attribute levels in each questionnaire. The sample of scenarios were then organised into pairwise profiles labelled ‘Choice A’ and ‘Choice B’, and participants were asked to choose between the pair of choices in each of the six choice sets. Furthermore, an opt-out option was included at the end of each choice set where patients were asked if, given the scenarios presented, they would still have the operation or prefer to remain in their current health state. This opt-out option was included as it reflects the voluntary nature of elective TKA in real life. For an example of a discrete choice task see Table 2.

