### Statistical analysis

Statistical analysis will be by intention-to-treat. Categorical variables will be analysed using chi-squared tests (or Fisher’s exact test for small samples) while continuous variables will be analysed using *t* tests (parametric) and Mann-Whitney (non-parametric) tests for symmetrically and asymmetrically distributed data, respectively. The significance of differences in dichotomous data will be tested using generalised estimating equations or a linear mixed model. If there are chance imbalances in baseline patient characteristics hypothesised to influence the main outcomes, then statistical techniques that allow adjustment for confounding variables will be used as secondary analyses. DCE data will be analysed based on extensions to logistic regression, including multinomial logit models, mixed logit models and generalised multinomial logit models [45]. If there is more than 5 % missing data, sensitivity analysis allowing for different assumptions, such as the best or worst possible scenario, will also be reported for the main outcomes of the study. Cohen’s kappa coefficient will be used to assess concordance between surgeon and patient expectations.

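### A/B choices alone, coded categorically, leave no degree of freedom for a position constant or a fit check in the discrete choice experiment (12 pairs, 12 level effects)

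*Protocol article*

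**What the plan says.** All references are to the protocol article.

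- Attributes and levels: "This resulted in six attributes, with three levels defined for each attribute (Table 1"). Four attributes are graded none, moderate or severe. The two risk attributes are numerical (0, 7, 13 % and 0, 10, 21 %).
- DCE experimental design: the attributes "give rise to a possible combination of 729 (3^6^) treatment outcome scenarios", from which an efficient fraction was drawn. "Two versions of the DCE questionnaire were generated, each containing six different choice sets", with the same attributes "but different attribute levels in each questionnaire". Scenarios were "organised into pairwise profiles labelled ‘Choice A’ and ‘Choice B".
- The same section adds a second response in every set: "an opt-out option was included at the end of each choice set where patients were asked if, given the scenarios presented, they would still have" surgery, as against staying as they are.
- Statistical analysis: "DCE data will be analysed based on extensions to logistic regression, including multinomial logit models, mixed logit models and generalised multinomial logit models". It does not give the coding of the levels, the constants to be fitted or the way the opt-out enters the model.
- Sample size: 66 patients per arm. Only the intervention arm completes the choice task.
- Background, aim 1: the choice data are to show how patients balance risks and benefits.

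**The concern.** Each distinct pair supplies one independent A-versus-B choice probability, however many patients answer it. Twelve pairs therefore support at most twelve parameters in a model of the A/B choices, and the categorical main effects use all twelve. Some respondents lean towards the first or left-hand option. If that lean exists and each profile always sits in the same position, a saturated model reproduces it exactly by shifting the level effects, and no fit statistic from that model shows it. The estimated trade-offs for aim 1 would then mix preference with position. The subgroup questions the article raises (previous knee replacement, patient characteristics) would share the problem if the habit differed between groups.

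**Working it through.** **Inputs.** Six attributes with three levels each (Attributes and levels); two versions of six different pairs plus an opt-out in each set (DCE experimental design); 66 intervention patients (Sample size). Assumed: an equal split between versions, 66 / 2 = 33 patients each.

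**The plan's own figure.** 3^6 = 729 scenarios; reproduced.

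**Counting parameters against equations**

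| Analysis | Equations | Parameters | Spare |
|---|---|---|---|
| A/B only, all categorical | 12 x (2 - 1) = 12 | 6 x 2 = 12 | 0 |
| The same plus a Choice A constant | 12 | 12 + 1 = 13 | -1 |
| A/B only, two risks linear, plus constant | 12 | 4 x 2 + 2 + 1 = 11 | 1 |
| A, B and opt-out, all categorical, plus A and opt-out constants | 12 x (3 - 1) = 24 | 12 + 2 = 14 | 10 |

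**Is the constant aliased in plausible designs?** The actual design is not shown, so 12-pair designs were generated.

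- Designs searched to minimise standard errors: the A-minus-B difference matrix had rank 12 without the constant and still rank 12 with it, in every design. The constant is fully aliased with the level effects.
- Random designs with no balance imposed: 1,792 of 1,943 showed the same pattern.
- Designs with each level shown equally often in A and in B: every column of the difference matrix sums to zero, so its rank is at most 11. All 2,160 such designs had rank 10 or 11, and the constant added one. Position is then separable, but at least one combination of level effects cannot be estimated from the A/B choices.

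**Size of the shift if aliased.** In searched designs with zero prior preferences, a position effect of 1 log-odds unit moved the level effects by 0.36 to 0.47 (root mean square) and by up to 0.72 to 0.90. Assume a position effect of 0.2 to 0.4, that is, A chosen about 55 to 60% of the time between equal profiles. The mean standard error of a level effect from 66 x 6 = 396 choices is about 0.148.

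- Typical level effect: 0.2 x 0.36 = 0.07 to 0.4 x 0.47 = 0.19, or about 0.5 to 1.3 standard errors.
- Worst-affected level effect: 0.2 x 0.72 = 0.14 to 0.4 x 0.90 = 0.36, or about 1 to 2.4 standard errors.

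**What the opt-out recovers.** With the opt-out as a third alternative, the information matrix had full rank 14 in 2,157 of 2,160 balanced and 1,942 of 1,943 unbalanced random designs, and in all the searched ones. The precision of the position constant varies (33 patients per version, assumed preference weights, opt-out share of about 20%):

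| Case | SE of constant | Power at 0.2 | Power at 0.4 |
|---|---|---|---|
| One unbalanced random design | 0.16 | 25% | 71% |
| Searched designs, opt-out as third alternative (median) | 0.47 | 7% | 14% |
| Searched designs, A/B first, then opt-out with its own scale | 0.23 | 14% | 42% |
| Same 12 pairs, position randomised | 0.10 | 48% | 97% |

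A second set of searched designs put the SE with the opt-out as third alternative at about 0.30 to 0.62.

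**The case against.** A reader might infer that any habit of choosing A must pass undetected into the preference estimates. The documents do not support that, for four reasons.

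- The opt-out is collected in every set and multinomial models are planned, so the constant can be identified. Weak power is not the same as non-identifiability.
- The article states no coding. With the numerical risks entered linearly, the constant is estimable from the A/B choices alone, with one degree of freedom to spare.
- The actual design is not shown, and in a position-balanced design the constant is not aliased.
- Each patient makes six choices, so strict always-A responding is visible. If 15% of patients always chose A, the all-A pattern would occur in about 16 to 17% of patients, against about 4% predicted by the saturated model.

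All four stand, and they limit the point to the conditional form given here. They do not remove it. A mild lean spread over many patients would not show as an all-A pattern. The opt-out figures assume one common constant, although the comparator is each patient's own current state. A position-balanced design loses a level-effect contrast from the A/B choices instead.

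Two further inferences should not be drawn. The article's silence on how versions are allocated is not a fault in a condensed report. The statement that "attributes were varied independently from one another across the scenarios" is also no error merely because 24 profiles do not divide evenly over nine level combinations (24 / 9 = 2.67): an efficient design need not be strictly orthogonal.

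It is also fair to say that the choice task is itself the randomised intervention and was pretested, which argues against replacing its pairs.

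**Conclusion.** The count is certain: 12 categorical level effects and 12 distinct pairs. The consequence is conditional. If the A/B choices are analysed alone, with all attributes categorical, positions fixed and a design that minimises standard errors, a position habit is absorbed into the level effects and the model offers no check of fit. For an assumed habit of 0.2 to 0.4 log-odds, the shift is about 0.5 to 1.3 standard errors in a typical level effect and up to about 2.4 in the worst. These sizes rest on generated designs, an equal split between versions and an assumed habit; the documents give none of these. Joint modelling of the opt-out or linear risk coding makes the constant estimable, but the opt-out route has little power for small effects at this sample size. The point concerns aim 1 only. The comparison of WOMAC and satisfaction between arms, and its sample size, are untouched. It is a worthwhile and nearly free improvement, not a fatal flaw.

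**What to change.** Keep the same 12 pretested pairs and six sets per patient.

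1. On the portable computer already used for the survey, randomise for each patient and each pair which profile is shown as Choice A, and store the position shown.
2. Fit a position constant in the choice models. Across patients each pair then appears in both orders, giving 24 ordered presentations against 13 parameters, and position is no longer confounded with the level effects.
3. Analyse the opt-out answer jointly with the A/B choice. This is needed for the fit check: randomising position frees the constant, but the 12 pairs still carry only 12 preference contrasts. The joint model has 10 spare equations. State in the analysis plan whether the risk attributes are categorical or linear.

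The cost is minor survey reprogramming, with no extra patients, sets or burden and no change to the content patients see. More versions of the questionnaire are optional and not required. They would allow a fit check within the A/B choices, but they bring in untested pairs and vary what the intervention arm receives. For patients surveyed with positions already fixed, only step 3 is available, and the position constant should then be reported with its standard error.
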